### Statistical design overview

The primary endpoint is the proportion of patients with an impairment in cognitive parameters 10 years after irradiation of skull base benign meningioma, or atypical meningioma.

As there are no available data in the literature concerning the prevalence of long-term cognitive disorders after radiotherapy treatment of skull base benign meningioma, or atypical meningioma, we assume that approximately 50% of patients will present an impairment of their cognitive functions 10 years after the end of irradiation. Using a 95% confidence interval with a width of 0.2 for a small sample size, a total of 93 patients is required.

In order to document the impact of brain irradiation on cognitive performances for each of the 3 radiotherapy modalities usually used in this indication, 31 patients are required in each of the 3 cohorts (IMRT, SRT, PRT).

In addition, a control group with 31 assessable participants free of brain disease will be constituted.

In order to anticipate 15% of subjects possibly non assessable, 36 subjects per each of the 4 cohorts will be enrolled, for a total of 108 patients and 36 participants free of brain disease.

Categorical variables will be summarized using numbers and proportions. Quantitative variables will be summarized using quartiles and range (mean and standard deviation for Gaussian-like variables). The pattern of missing data will be described.

Briefly, all outcomes will be analyzed based on intention-to-treat principle. For each cohort, the Intention to Treat (ITT) population is defined as all patients included in this radiation arm, regardless of whether eligibility criteria are met and whether or not radiation therapy is used.

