#### Secondary objectives

At the patient level: no comparison between arm is planned in analyses.

The Progression-Free Survival (PFS) time is defined as the time elapsed from treatment start to progression disease or death from any cause. Data of patients who did not experience event are censored at the last assessment date. PFS will be estimated by the Kaplan-Meier method. The evolution of health-related quality-of–life after irradiation will be described by mean and standard error, and compared across time by the Student t test for paired data.

With regard to radiotherapy parameters: in each cohort, the correlation between dosimetric data (quantitative data) and the occurrence of cognitive deterioration will be assessed by the non-parametric Wilcoxon Mann Whitney test.

With regard to brain MRI parameters: In each cohort, association between alterations or modifications of grey and white matters after irradiation on brain MRI and cognitive deterioration will be assessed by the exact Fisher test.

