**Patients**						
**Standard physical and neurological examination (Nano-scale)**		✓	✓ Weekly during radiotherapy		✓	✓
**Cognitive assessment** (by a trained neuropsychologist): - *Executive functions* - *Episodic memory* - *Working memory* - *Short-term memory* - *Attention/Information processing speed* - *Prospective memory (Mem-Pro* Clinic)		✓			✓	✓ **(at 3**,** 5**,** 7 and 10 years only)**
**Brain MRI** (standard follow-up):3DT1w, Diffusion (b = 0 and b = 1000 s.mm-2, 30 directions), Perfusion (Dynamic Susceptibility Contrast, DSC-MRI), 3DT1 Gadolinium, 3D Fluid Attenuated Inversion Recovery (FLAIR), Angiographic “time of flight” sequence (TOF)		✓			✓	✓
**Cognitive complaints**,** anxiety and depression assessment** *Fact-Cog* *- HADS* *MFI*		✓			✓	✓
**Quality-of-life assessment** *- EORTC QLQC30 + BN20*		✓			✓	✓
**Evaluation of the socio-professional** **reintegration**		✓			✓	✓
*At the discretion of the investigator*: Endocrinological, ophthalmological and audiometric evaluations		✓			✓ (12 months only)	✓
	*OPTIONAL*					
Blood sample banking		✓		✓	✓	✓
Participants free of brain disease						
	Baseline assessment (within 6 weeks before radiotherapy start)	6 and 12 months	Yearly up to 10 years			
**Cognitive assessment** (by a trained neuropsychologist): - *MoCA* - *Executive functions* - *Episodic memory* - *Working memory* - *Short-term memory* - *Attention/Information processing speed* - *Prospective memory (Mem-Pro* Clinic)	✓	✓	✓ **(at 3**,** 5**,** 7 and 10 years only)**			
**Cognitive complaints**,** anxiety and depression assessment** *Fact-Cog* - *HADS* - *MFI*	✓	✓	✓			
**Quality-of-life assessment** - *EORTC QLQC30*	✓	✓	✓			

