#### Follow up after irradiation

Evaluations will be realized **at 6 months**,** 1 year and every year until 10 years after the end of radiotherapy (**Table 2). Cognitive assessment will be performed only at 6 months, 1 year, 3 years, 5 years, 7 years and 10 years.

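### Quality of life at baseline and 11 later visits is compared by paired t tests, which use only patients with both values; a longitudinal model within each cohort would suit the schedule better

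*Protocol article*

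**What the plan says.** The statistical section Secondary objectives of the Protocol article fixes the quality-of-life analysis in one sentence. The outcome "will be described by mean and standard error" and is then "compared across time by the Student t test for paired data". No other test or model is named for it. The same section rules out comparisons between arms, so these are changes within patients, cohort by cohort.

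Table 2 schedules the questionnaires ("EORTC QLQC30 + BN20" for patients) at baseline, at 6 and 12 months, and yearly to 10 years. Follow up after irradiation agrees: evaluations take place at 6 months, "1 year and every year until 10 years after the end of radiotherapy". Only the neuropsychological tests have a thinner schedule ("Cognitive assessment will be performed only at 6 months, 1 year, 3 years, 5 years, 7 years and 10 years"), so quality of life keeps every visit.

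On numbers, Statistical design overview states that "36 subjects per each of the 4 cohorts will be enrolled, for a total of 108 patients and 36 participants free of brain disease", with 15% allowed for as non-assessable. It applies the intention-to-treat principle to all outcomes. On incomplete data it says: "The pattern of missing data will be described".

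**The concern.** The stated objective is how quality of life evolves after irradiation. A paired t test compares two time points, so using it across 12 time points means either repeating it or leaving most of the series out of the test.

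Two consequences follow. First, each test uses only patients observed at both of its visits. A patient who leaves after year 5 contributes nothing to the year-10 comparison, although the earlier scores carry information about the likely course. If those who leave were already doing worse, the late comparison looks too favourable. Second, repeated tests at an unadjusted level produce chance findings somewhere in the series more often than the nominal level suggests.

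The choice of test is written into the article, so this is a stated method that can be improved and not a detail left for the analysis plan.

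**Working it through.** The article gives no figure for this analysis, so there is none to reproduce. The significance level (5% two-sided), the correlations between visits and the dropout mechanism below are assumptions.

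**1. Number of visits.** 6 months, plus years 1 to 10: 1 + 10 = 11 after baseline, or 12 time points in all. Possible pairs: 12 × 11 / 2 = 66.

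**2. Pairs available.** With 36 enrolled and loss d spread evenly over 10 years, pairs with baseline at year t number 36 × (1 − d × t/10).
- d = 15%: 36 × (1 − 0.15 × 0.05) = 35.7 at 6 months; 36 × 0.85 = 30.6 at year 10.
- d = 30%: 36 × 0.70 = 25.2 at year 10.

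**3. Effect of dropout related to earlier quality of life.** Simulation with 36 patients, 12 time points, correlation 0.6 between any two visits, higher scores better and no true change. From year 1 on, the log-odds of leaving rise by 1 for each SD of worsening from baseline at the previous visit. There were 800 runs per row; bias is in units of the SD of a score at one visit.

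| Lost by year 10 | Bias, paired test | Rejection rate of that test (nominal 5%) | Bias, likelihood-based estimate |
|---|---|---|---|
| 14.2% | +0.057 | 7.0% | 0.001 |
| 30.0% | +0.117 | 9.9% | −0.009 |

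The paired estimates vary between runs with SD 0.162 and 0.175, so the simulation error of the bias is about 0.162/√800 ≈ 0.006 and 0.175/√800 ≈ 0.006. The paired bias is clearly non-zero; the likelihood-based bias is within about 1.5 simulation errors of zero. Relative to sampling error in one cohort, the paired bias is 0.057/0.162 ≈ 0.35 and 0.117/0.175 ≈ 0.67 standard errors. The likelihood-based estimate used the true covariance; with an estimated one the result would be somewhat less clean.

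**4. False positives if all 11 visits are tested against baseline at 5%.**
- Independent tests: 1 − 0.95^11 = 43% per scale and cohort; 1 − 0.95^33 = 82% over three cohorts.
- Expected number per scale: 11 × 0.05 = 0.55 per cohort; 33 × 0.05 = 1.65 over three cohorts. These do not depend on correlation.
- The tests are not independent, because they share the baseline value. With equal correlation r between visits, each change has variance 2(1 − r) and two changes have covariance 1 − r, so they correlate at 0.5 whatever r is.

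Simulation with 31 complete patients, no true change and 10,000 runs per row:

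| Correlation between visits | At least one of 11, one cohort | Over three cohorts, 1 − (1 − p)^3 |
|---|---|---|
| Equal, 0.3 | 31.2% | 67.4% |
| Equal, 0.6 | 30.6% | 66.6% |
| Equal, 0.8 | 31.3% | 67.5% |
| Decaying, 0.6 per year | 28.6% | 63.6% |
| Decaying, 0.8 per year | 25.8% | 59.1% |
| Decaying, 0.9 per year | 24.5% | 57.0% |

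**5. What removes the excess.** In the same runs, one global test of time with an unrestricted covariance on complete data rejected in 4.7–5.1%. The gain comes from making one test in place of 11. The result does not validate every mixed model, and visit-by-visit contrasts from a mixed model would still need adjustment or a descriptive label.

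**The case against.** The best defence is that quality of life is a secondary, within-cohort outcome, described first by means and standard errors, with no success criterion attached. The primary analysis is a proportion with a confidence interval in each cohort and does not depend on it. Unadjusted visit-wise tests are common in such a setting. A condensed article may also leave the pairs to be compared and any adjustment to a fuller document, and a single prespecified pair would remove the multiplicity point. All of this stands, and it limits the weight of the point. It does not rescue the paired test itself, which the article does fix and which would still discard incomplete pairs.

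Stronger readings are tempting, but the article does not support them:
- **That the plan carries a 43% or 82% false-positive risk.** Those are the independent-test figures, and the 11-test family and the 5% level are inferred. Pooling three cohorts is also open to question when each is analysed alone.
- **That late visits will contain the healthier patients.** The article does not show this. Patients are under 65, have WHO status 0 or 1 and an expected survival above 10 years, and those who stop treatment only remain in follow-up.
- **That year 10 is the required focus.** That horizon belongs to the cognitive endpoint; for quality of life the objective is evolution over time.
- **That a mixed model cures the multiplicity.** It does not; prespecifying one test does, and that could be done with a paired test too.
- **That the other scales are wrongly analysed.** The section states no test for anxiety and depression, fatigue or cognitive complaints, so there is no stated method to fault.

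**Conclusion.** The point holds as a moderate weakness in a stated method. The paired t test is poorly matched to a series of 12 time points over 10 years.

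- **Selective loss:** a year-10 bias of about 0.06 SD near the planned 15% loss and 0.12 SD at 30%, towards understating deterioration. This is conditional on dropout that depends on earlier observed scores. If dropout is unrelated to quality of life, the paired test loses precision but is not biased. If it depends on unobserved scores, the mixed model is not protected either.
- **False positives:** about 24–31% for at least one per scale and cohort, and 1.65 expected per scale over three cohorts, conditional on testing every visit against baseline at 5%. Analysing several scales adds to this.

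The primary endpoint is untouched.

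**What to change.** In the statistical section Secondary objectives, replace the paired t tests with a linear mixed model for each quality-of-life scale:
- fitted separately in each cohort, in keeping with the absence of comparisons between arms;
- using all observed visits, with visit as a categorical effect and the baseline score as a covariate;
- with a parsimonious covariance, such as random intercept and slope or a correlation that decays with time, because about 36 patients cannot reliably support an unstructured matrix over this many visits.

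As a separate step, prespecify one global test of time or one key contrast per cohort and name the scale it applies to. Change at 10 years with a 95% confidence interval is one option; the choice is the sponsor's. Report all other visits as descriptive estimates with confidence intervals.

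The cost is a change of wording and slightly more analysis work, with no new data or patients. The downside is that a covariance structure has to be chosen in advance. Inclusions began in 2023, so no 10-year value can exist before about 2033, and the change can still be made without knowledge of the late results.

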**With regard to radiotherapy parameters**:
To evaluate, according to 3 modalities of brain irradiation (PRT, SRT, IMRT), the correlation between dosimetric data and cognitive deterioration onset.To build tumoral control probability (TCP) and normal tissue complication probability (NTCP) on the basis of the prospective evaluations of patients.

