#### Irradiation

Radiotherapy will be initiated within 6 weeks after inclusion and will last 7 weeks at maximum.

The localization of radiotherapy treatment will depend on the decided radiotherapy modality:

Patients in the IMRT and SRT cohorts will thus be treated in the investigator center.Patients in the PRT cohort will be addressed by the investigator, as usual in case of treatment by proton-therapy, to the the site of proton therapy of Caen. The dosimetry and the pretreatment imagery will be performed by the proton therapy center.

All patients will have to complete the brain irradiation schedule in less than 45 days, from the first day of irradiation to the last day. Treatment should not be protracted over more than 45 days. Delineation should be performed on a 1-millimeter scanner and patients should be immobilized with a thermoplastic mask. Baseline MRI should be registered with the dosimetric scan to allow an accurate delineation of the target and organs at risks (OAR).

For grade I meningioma, prescription dose will be 50-54GyRBE (1,8–2 Gy per fraction) for IMRT and PRT cohorts or 25 Gy (5 Gy per fraction) (D2% between 125 and 140%) for SRT cohort.

For grade II meningioma, prescription dose will be 54-60GyRBE (1,8–2 Gy per fraction) for IMRT and PRT cohorts. SRT is not allowed.

Details about OAR delineations and dosimetric dose constraints are given in the Supplementary material n°1.

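### In the IMRT and PRT cohorts prescription dose is set by tumour grade, yet the stated dose-cognition test takes no account of grade, so a grade effect could be read as a dose effect

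*Protocol article*

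**What the plan says.** All places are in the protocol article.

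- **Dose rule (Irradiation).** For IMRT and PRT: "For grade I meningioma, prescription dose will be 50-54GyRBE" and "For grade II meningioma, prescription dose will be 54-60GyRBE". For SRT there is a single prescription level, "25 Gy (5 Gy per fraction) (D2% between 125 and 140%) for SRT cohort", given in the grade I paragraph. For grade II, "SRT is not allowed".
- **Who is enrolled (Eligibility criteria).** Both grades are eligible. A radiological diagnosis is accepted when biopsy is declined, so some patients will have no histological grade.
- **Objective (Secondary objectives and endpoints, radiotherapy parameters).** By modality, to evaluate "the correlation between dosimetric data and cognitive deterioration onset". A separate sentence sets the aim "To build tumoral control probability (TCP) and normal tissue complication probability (NTCP) on the basis of the prospective evaluations of patients".
- **Analysis (Statistical design overview, Secondary objectives).** The rule, applied to every cohort separately, is that "the correlation between dosimetric data (quantitative data) and the occurrence of cognitive deterioration will be assessed by the non-parametric Wilcoxon Mann Whitney test". No stratum or covariate is given.
- **Factors of interest (Hypothesis and expected clinical outcomes).** The list for the dose-cognition relationship covers dosimetry, age at treatment, brain region, radiation type and dose per fraction. Grade is not on it.
- **Cohort size (Statistical design overview).** 31 assessable patients per cohort, with 50% impaired at 10 years assumed.

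**The concern.** A Wilcoxon Mann Whitney test compares the dose distribution of patients who deteriorated with that of patients who did not. In a cohort that mixes grades under this dose rule, a patient above 54 GyRBE is grade II and a patient below it is grade I. Anything that makes grade II patients deteriorate more often apart from dose, such as recurrence, further treatment or tumour extent, would raise the dose ranks of the deteriorated group and could produce a significant result with no dose effect at all.

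The article expects its results to help spare important brain regions and to inform the choice of technique. A dose signal that cannot be told apart from grade would be a poor guide for either. The test is named explicitly, so this is a stated method that conflicts with the protocol's own dose rule, and not a detail left to a fuller document.

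**Working it through.** **1. Cohort size.** The article's total reproduces with a Wilson interval at p = 0.5: n = z²/w² − z² = 3.8415/0.04 − 3.8415 = 92.2, rounded up to 93, and 93/3 = 31 per cohort. This figure is not in dispute; 31 is used below.

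**2. How closely prescription dose follows grade.** Assume dose is uniform within each grade's range. Grade I then has mean 52 and variance 4²/12 = 1.33; grade II has mean 57 and variance 6²/12 = 3. With grade II share s:

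r² = 25·s(1−s) / [25·s(1−s) + 1.33(1−s) + 3s]

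- s = 0.1: 2.25/3.75, r = 0.77
- s = 0.2: 4.00/5.67, r = 0.84
- s = 0.3: 5.25/7.08, r = 0.86
- s = 0.5: 6.25/8.42, r = 0.86

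**3. False positives for prescription dose.** Simulated cohorts of 31 (3,000 per setting), dose as above, deterioration depending on grade only, 50% deterioration overall, two-sided 5% level. The stratified comparator is the van Elteren test: the sum over grades of [W − n₁(N+1)/2]/(N+1), divided by its permutation standard error. Here W is the dose rank sum of the n₁ deteriorated patients among the N patients of that grade. The table gives the rejection rate of the planned unadjusted test, by assumed grade II minus grade I difference in deterioration:

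| Grade II share | 0 points | 10 | 20 | 30 | 40 |
|---|---|---|---|---|---|
| 10% | 5% | 4% | 6% | 8% | 10% |
| 20% | 5% | 6% | 9% | 14% | 22% |
| 30% | 5% | 6% | 12% | 21% | 35% |
| 50% | 5% | 8% | 15% | 28% | 46% |

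The stratified test rejects in 4.4-5.5% of cohorts in every cell. Fixing the rates at 40% (grade I) and 70% (grade II), with half the cohort grade II, gives 29% for the unadjusted test.

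**4. False positives for organ doses.** The dosimetric data need not be prescription dose. Repeating the exercise with a normally distributed dose whose correlation with grade is assumed to be 0.2 or 0.4 (20-30 point difference, 30-50% grade II), the unadjusted test rejects in about 5% and about 6-10% of cohorts respectively.

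**5. SRT cohort.** Grade II is excluded and there is one prescription level, so grade does not vary and cannot confound.

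**6. Price of stratifying.** Suppose prescription dose truly acts, with a log-odds slope of 0.3-0.4 per Gy, and grade has no effect of its own. At n = 31 and 30-50% grade II, power is about 47-79% for the unadjusted test and about 14-26% for the van Elteren test. Stratifying leaves only the variation within ranges 4 and 6 Gy wide.

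**The case against.** **Dosimetric data are broader than prescription dose.** The article points to doses in structures such as the hippocampi and frontal lobe, which also depend on tumour site, volume and beam arrangement. This stands. The 12-29% applies to prescription dose and to measures that track it closely; for loosely linked organ doses the inflation is small.

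**No grade effect on cognition is documented.** This also stands. Without an effect of grade apart from dose, the planned test keeps its 5% level, as the zero-difference column shows. The article gives no reason to assume such an effect is absent over 10 years, so the protection is still worth having.

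**Stratifying costs much of the power.** True for prescription dose, and a good reason not to discard the unadjusted test. But the extra power of that test comes from the contrast between grades, which is exactly the part that cannot be attributed to dose.

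**Grade is not always histological.** Correct, but prescribing by grade requires every IMRT and PRT patient to be assigned one, so a stratum exists.

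**Stronger readings a reader might infer.** One is that every cohort is affected; the exclusion of grade II from SRT rules that out. Another is that the tumour control model is planned without grade and would show control falling with dose. The article states only the aim of building TCP and NTCP models. It names no predictors and does not leave grade out, and the reference to three modalities belongs to the neighbouring dose-cognition objective. Model covariates are what an article commonly leaves to the full protocol, so no finding and no size can be attached to TCP.

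**Conclusion.** The point holds for the dose-cognition test in the IMRT and PRT cohorts only. There the dose rule and the unadjusted test together mean that prescription dose and grade cannot be separated, and a grade effect could, not necessarily would, be reported as a dose effect.

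For prescription dose the false-positive rate is about 12-29% instead of 5%. That rests on assumed grade differences of 20-30 points, a grade II share of 30-50% and doses spread evenly within each range. The article gives none of these. With a 10% grade II share, or with organ doses weakly linked to grade, the rate is about 10% or less. This is a secondary analysis; the primary estimate and the sample size are untouched.

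**What to change.** In the Secondary objectives analysis text, for the IMRT and PRT cohorts:

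- Report a grade-stratified (van Elteren) or grade-adjusted (logistic, grade as covariate) dose-cognition analysis beside the planned Wilcoxon Mann Whitney test.
- Claim a dose effect only if it holds within grade.
- Place patients without histology in the grade used to prescribe their treatment.
- Report a null within-grade result as inconclusive, not as evidence of no dose effect.

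The SRT analysis can stay as written.

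The cost is a change of wording; no new data are needed, since grade already drives the prescription. The real downside is the low within-grade power for prescription dose shown above. That limit comes from how little dose varies apart from grade in this design, and the choice of test cannot remove it.

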### Primary objectives and endpoints

The primary objective is to report long-term cognitive deterioration among patients with a diagnosis of skull base benign meningioma, or atypical meningioma treated by fractionated proton-therapy (PRT) or hypo-fractionated stereotactic radiotherapy (SRT) or normo-fractionated intensity-modulated radiotherapy (IMRT), 10 years after the end of irradiation.

The primary endpoint is the proportion of patients with an impairment in cognitive parameters 10 years after irradiation of skull base benign meningioma, or atypical meningioma.

Cognitive impairment is defined as a clinically significant deterioration, in comparison with baseline evaluation (before brain irradiation), in neurocognitive test scores, grouped into five cognitive domains:

Attention/information processing speed,executive functioning,episodic memory,working memory,short term memory.

Deterioration is either defined as (i) the occurrence of cognitive impairment (a total of ≥ 5 impaired z-scores, as considered in Douw et al. 2009) among patients who were not cognitively impaired at baseline, or (ii) the worsening of cognitive impairment (≥ 2 supplementary impaired z-scores) among patients who were already cognitively impaired at baseline.

Scores will be converted to z-scores by subtracting mean and dividing by standard deviation (SD) of data of participants free of brain disease from the control group. A z-score of at least 2 SD below normative data is defined as impaired.

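### The dose and MRI tests against cognitive deterioration carry no baseline cognitive term, although the event rule sets very unequal hurdles by baseline count of impaired scores

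*Protocol article*

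**What the plan says.** Under Secondary objectives in the statistical section, the protocol article states, for the cohorts taken separately, that "the correlation between dosimetric data (quantitative data) and the occurrence of cognitive deterioration will be assessed by the non-parametric Wilcoxon Mann Whitney test". For MRI, the association between grey or white matter change "after irradiation on brain MRI and cognitive deterioration will be assessed by the exact Fisher test". Neither sentence names a covariate or a stratum.

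The outcome of both tests is defined under Primary objectives and endpoints. A single score counts as impaired by this rule: "A z-score of at least 2 SD below normative data is defined as impaired", the reference being the control group. Deterioration then has two routes:

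- "the occurrence of cognitive impairment (a total of ≥ 5 impaired z-scores", which applies "among patients who were not cognitively impaired at baseline";
- "the worsening of cognitive impairment (≥ 2 supplementary impaired z-scores) among patients who were already cognitively impaired at baseline".

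Table 2 schedules the full cognitive battery at baseline for every patient, so baseline scores will be available.

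**The concern.** For patients who start unimpaired, the event means crossing a fixed line, and the distance to that line depends on where they start. Two patients with the same true decline can have very different chances of being flagged. Referring the event to baseline does not adjust for baseline in an association test. This rule is what makes the flag depend on the baseline count.

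Two consequences follow. The spread in baseline cognition enters the unadjusted tests as noise and costs power. And if patients who start with more deficits also receive more dose to a region, for instance because of tumour size or location, the baseline difference can show up as a dose or MRI association. With the opposite sign, a real effect can be hidden. The Hypothesis section wants the study to inform which brain zones to preserve, so both matter for interpretation.

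**Working it through.** **Inputs from the article.** Expected event proportion 0.50; 31 assessable patients per cohort; the two-route event rule; unadjusted tests within cohort.

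**The plan's own figure.** At p = 0.5 the full width of a 95% Wilson interval is z/√(n + z²). Setting it to 0.2 gives n = (1.96/0.2)² − 1.96² = 96.04 − 3.84 = 92.2, hence 93, as stated. 93/3 = 31 per cohort. Expected events per cohort: 0.5 × 31 = 15.5. The article gives no power or effect size for the association tests.

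**Hurdle by baseline count c.** New impaired scores needed = 5 − c for c = 0 to 4, and 2 for c ≥ 5:

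| Baseline count | 0 | 1 | 2 | 3 | 4 | 5 or more |
|---|---|---|---|---|---|---|
| New impaired scores needed | 5 | 4 | 3 | 2 | 1 | 2 |

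**Assumptions for simulation.** The article does not give the number of scores, the baseline distribution, the dose–baseline correlation or the size of a dose effect.

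- *Set-up A:* 20 scores, retest reliability 0.8, general factor 0.35, patients on average 0.5 SD below controls (extra SD 0.6), decline 1 SD (SD 0.5). This gives 53% events.
- *Set-up B:* 20 scores, 13% impaired at baseline, event rate tuned to about 50%. Variants used 15 to 25 scores and 2 to 35% impaired at baseline.

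All tests are two-sided at 0.05 with n = 31. Ranges reflect repeat runs and variants of the assumptions.

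**Step 1: event probability by baseline count, decline unrelated to dose.**

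- A: 26% at count 0, 67–69% at 1–2, 91% at 3–4, 90–91% at 5 or more.
- B: 0.26, 0.46, 0.62, 0.73 and 0.81 at counts 0 to 4, and 0.77 at 5 or more. Across the variants, count 0 ranges over 0.18–0.38 and count 4 over 0.72–0.87.

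**Step 2: no dose effect, rejection rate.**

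| Dose–baseline correlation | Wilcoxon, A | Wilcoxon, B | Fisher, A (median split) | Fisher, B (binary marker) | Logistic score test adjusted for mean baseline z, A |
|---|---|---|---|---|---|
| 0 | 4–5% | 5% | 3% | 3% | 5–6% |
| 0.3 | 10–16% | 11% | 6% | 6% | 5–6% |
| 0.5 | 21–38% | 23% | 11% | 13% | 5–6% |

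The upper Wilcoxon values in A (16% and 38%) arise when dose is correlated with the whole baseline deficit. The lower ones (10% and 21%) arise when it is correlated only with the patients' extra deficit relative to controls. The Fisher figures belong to this narrower reading. Over the variants of B, Wilcoxon gives about 9–12% at 0.3 and 14–25% at 0.5.

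**Step 3: real dose effect, correlation 0 (set-up A).**

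| Extra decline per SD of dose | Wilcoxon | Logistic, mean baseline z |
|---|---|---|
| 0.4 SD | 39–43% | 62–64% |
| 0.3 SD | 25–26% | 43–44% |

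**Step 4: real dose effect of 0.3 SD, opposite-sign correlation.** In B, Wilcoxon power falls from 30% at correlation 0 to 12% at −0.3 and 5% at −0.5. A Wilcoxon test stratified by count (0–1, 2–4, 5 or more) gives 30%, 20% and 12%. In A, with dose correlated at −0.3 with the whole deficit, power is 7% unadjusted and 42% adjusted for mean z.

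**Step 5: which adjustment.** In A at 0.4 SD and correlation 0, power is 64% adjusting for mean z, 52% adjusting for the count, 47% with the stratified Wilcoxon and 39% unadjusted. With no dose effect and correlation 0.5, count adjustment still rejects in 12.5% and stratification in 9.5% (7–12% over the variants of B). An ordinary adjusted logistic model was slightly liberal at n = 31: 6–8% with no dose effect and no correlation.

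**The case against.** The strongest reply is that the premise for bias is not in the document. Inflation needs a correlation between dose and baseline deficit inside a cohort. The abstract links tumour size to the choice of technique, which is a matter between cohorts, whereas these tests run within cohorts. The eligibility criteria (skull base only, performance status 0–1, age under 65, ability to follow the protocol) may also narrow the baseline spread. At zero correlation the planned Wilcoxon test keeps its level. All of this stands, so the false-positive figures are conditional. The power loss in Step 3 does not need the correlation.

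A reader might infer that the baseline count is the strongest driver of the event. The documents do not show that, and the simulations do not support it as a general statement. In A the count correlates with the event at 0.41 and true decline at 0.43–0.44; in B the figures are 0.23–0.35 against 0.56–0.69. Nor is baseline wholly ignored, since the event is defined against it. A reader might also infer that false effects and masked effects occur together through confounding. They need opposite signs of the correlation.

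The power gain depends on the adjuster: in B the coarsely stratified Wilcoxon gained nothing at zero correlation (30% under both). The MRI case is weaker too, because Fisher is conservative at this size and a link between baseline deficit and MRI change is likewise assumed.

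Finally, the planned NTCP modelling or a fuller analysis plan may include adjusted models. That is possible, and omitted covariates there are no finding. But the article names these two tests, and their poor fit with the event rule is visible as stated.

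**Conclusion.** The point holds as a mismatch between two stated choices: an event rule with hurdles of one to five new impaired scores depending on baseline, and association tests that carry no baseline term. Under the assumed settings at n = 31, the cost with unrelated dose and baseline is power of about 40% instead of 63% at 0.4 SD per SD of dose, and about 26% instead of 44% at 0.3 SD. If a within-cohort correlation exists, a true null is rejected by the Wilcoxon test in about 10–16% of trials at 0.3 and 21–38% at 0.5, with somewhat lower values in some variants (about 9% and 14%). Fisher reaches about 6% and 11–13% under the narrower reading of that correlation. An opposite-sign correlation hides real effects.

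The documents do not support saying that the planned tests will produce false dose effects, only that they are unprotected against them. These are secondary analyses, and the primary per-cohort proportion is untouched. The change is worth making because it is cheap and the 10-year outcomes are still years away.

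**What to change.** In the Secondary objectives part of the statistical section, for each dose metric and for MRI change, add a logistic analysis of deterioration adjusted for mean baseline z-score, using a small-sample method (score test, exact or Firth-penalised). State that it is interpreted ahead of the unadjusted tests, keep the Wilcoxon and Fisher results as descriptive, and label all of these analyses exploratory. Adjustment for the baseline count, or a Wilcoxon test stratified by coarse count groups (van Elteren), can be a secondary option only, since it leaves residual confounding and recovers less power.

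Cost: analysis wording, with no new data or visits. The downside is one extra parameter with about 15 events per cohort, which is why an ordinary large-sample logistic test should not be the default.
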